# Hand-Assisted laparoscopic donor nephrectomy PERiumbilical versus Pfannenstiel incision and return to normal physical ACTivity (HAPERPACT): study protocol for a randomized controlled trial

**DOI:** 10.1186/s13063-018-2775-4

**Published:** 2018-07-13

**Keywords:** Living donor, Hand-assisted laparoscopy, Physical activity, Randomized clinical trial

## Abstract

**Background:**

Hand-assisted laparoscopic living donor nephrectomy (HALDN) using a periumbilical or Pfannenstiel incision was developed to improve donor outcome after a kidney transplant. The aim of this study was to investigate two methods of hand assistance and kidney removal during HALDN and their effect on the time it takes for the donor to return to normal physical activity.

**Methods/design:**

This study was initiated in November 2017 and is expected to last for 2 years. To be eligible for the study, donors must be more than 20 years of age and must not be receiving permanent pain therapy. Only donors with a single artery and vein in the graft are being enrolled in this trial. Donors with infections or scars in the periumbilical or hypogastric area, bleeding disorders, chronic use of immunosuppressive agents, or active infection will be excluded. Donors will be randomly allocated to either a control arm (periumbilical incision) or an intervention arm (Pfannenstiel incision). The sample size was calculated as 26 organ donors in each group. The primary endpoint is the number of days it takes the donor to return to normal physical activity (up to 4 weeks after the operation). Secondary endpoints are intraoperative outcomes, including estimated blood loss, warm ischemia time, and duration of the operation. Postoperative pain will be assessed using the visual analog scale, rescue analgesic use, and peak expiratory flow rate. Length of hospital stay, physical activity score, time to return to work, donor satisfaction, cosmetic score, postoperative complications, and all-cause mortality in living donors will also be reported. Delayed graft function, primary non-function, serum creatinine levels, and glomerular filtration rate will also be assessed in the recipients after transplantation.

**Discussion:**

This is the first randomized controlled trial to compare the time it takes the living donor to return to normal physical activity after HALDN using two different types of incision. The comprehensive findings of this study will help decide which nephrectomy procedure is best for living donors with regard to patient comfort and satisfaction as well as graft function in the recipient after transplantation.

**Trial registration:**

ClinicalTrials.gov, NCT03317184. Registered on 23 October 2017.

**Electronic supplementary material:**

The online version of this article (10.1186/s13063-018-2775-4) contains supplementary material, which is available to authorized users.

## Background

Despite remarkable improvements in kidney procurement from deceased donors, the demand for organs is still higher than the number of available kidneys. The use of living donor kidney transplantation (LDKT) has been increased in an attempt to overcome the organ shortage [1–4]. The main concern of LDKT is that a healthy person undergoes major surgery to supply an organ, which may have serious adverse effects. Therefore, a safe nephrectomy method with a low complication rate is just as important as ensuring good graft quality after transplantation [3, 5].

Open donor nephrectomy was the most common technique for kidney removal before laparoscopic surgery was developed [6, 7]. Laparoscopic nephrectomy has obvious intraoperative and postoperative advantages over open surgery in terms of blood loss, postoperative pain, duration of hospital stay, and convalescence [8–10]. In 1998, shortly after the development of commercial ports, Wolf et al. [11] reported the hand-assisted laparoscopic living donor nephrectomy (HALDN) technique. Since then, this technique has been widely adopted [12]. HALDN offers better manual control of bleeding, a shorter learning curve, less kidney traction, faster kidney extraction, and shorter warm ischemia times [7, 11–13]. Nowadays, HALDN is one of the most commonly applied surgical procedures, and it has a relatively low complication rate [13].

HALDN is usually performed using a periumbilical or Pfannenstiel incision for hand-port placement and kidney extraction [14]. So far, several retrospective and non-randomized prospective studies have compared periumbilical and Pfannenstiel incisions [13, 15–18]. While some studies have shown better donor outcomes for periumbilical incision with regard to blood loss, warm ischemia time, duration of the surgery, and postoperative pain [15, 17, 18], Pfannenstiel incision is associated with fewer early and long-term wound complications and better cosmetic outcomes [13, 16]. Donors were also able to return to work more quickly after a Pfannenstiel incision [15]. However, these conclusions were the results of retrospective or non-randomized prospective studies. To our knowledge, the use of these two different incisions during HALDN has not been compared in a randomized controlled trial (RCT).

In this RCT, we are investigating the effect of two different hand-assistance and kidney removal techniques during HALDN, using periumbilical and Pfannenstiel incisions, on the time it takes for donors to return to normal physical activity. We will also analyze graft function in the recipient after transplantation.

## Methods/design

### Setting

This is a single-center, expert-based RCT. The trial is now underway at the Division of Transplantation Surgery, Department of General, Visceral, and Transplantation Surgery, University of Heidelberg. It was initiated in November 2017, and it is expected to progress for 2 years. The trial was registered at ClinicalTrials.gov under registration number NCT03317184 on October 23, 2017. The Standard Protocol Items: Recommendations for Interventional Trials (SPIRIT) checklist is provided in Additional file 1.

### Patient recruitment

The study protocol was accepted by the independent Ethics Committee of the University of Heidelberg (registration number S-291/2017). As shown in the study flow chart (Fig. 1), all kidney donors (including left and right kidneys) are currently being screened for eligibility criteria. To be eligible for the study, living donors must be more than 20 years of age and must not be receiving permanent pain therapy. Only donors with a single artery and vein in the graft are being enrolled in this trial. Donors with infections or scars in the periumbilical or hypogastric area, bleeding disorders, chronic use of immunosuppressive agents, and active infection are being excluded. All included donors will be informed about periumbilical and Pfannenstiel incisions for HALDN, as well as their potential benefits and side effects. Eligible donors will receive a written informed consent form. Donors who sign the informed consent form will be included in the study. Reasons for exclusion from the Hand-Assisted laparoscopic donor nephrectomy PERiumbilical versus Pfannenstiel incision and return to normal physical ACTivity (HAPERPACT) trial will be documented and explained in the screening form. After baseline assessments and assessment of eligibility, the patient will be randomized to the periumbilical or Pfannenstiel arm.

**Fig. 1 Fig1:**
[figure not shown]
Study design flow chart. *Preoperative assessments including date of birth, gender, weight (kg), height (cm), and American Society of Anesthesiologists score. **Return to normal physical activity will be self-assessed using the Katz Basic Activities of Daily Living self-maintenance questionnaire during the first 4 postoperative weeks until all normal activities are recovered. *PEFR* peak expiratory flow rate, *PNF* primary non-function, *DGF* delayed graft function, *GFR* glomerular filtration rate, *IPAQ-SF* International Physical Activity Questionnaire-Short Form

### Outcome measures

During the HAPERPACT trial, donors will be monitored before surgery, intraoperatively, on postoperative days (PODs) 1, 2, 3, and at discharge. After discharge, patients will be visited during postoperative weeks (POWs) 2, 4, and 8. During the first four POWs, donors will complete a self-administered questionnaire every day. Demographic and baseline clinical data, intraoperative findings, and postoperative results will be recorded (Fig. 2). Furthermore, graft function will be assessed until the fourth POW.

**Fig. 2 Fig2:**
[figure not shown]
HAPERPACT trial design according to the Standard Protocol Items: Recommendations for Interventional Trials (SPIRIT) checklist

To enhance participant retention and to avoid loss to follow-up, we call the patients during the follow-up period to remind them of scheduled visits and to arrange appointments. When a patient is not able to participate in a follow-up visit, we will speak with the patient on the telephone and ask him/her to send us a photo of the incision.

#### Primary endpoint

Patients will complete the Katz Basic Activities of Daily Living (ADL) self-maintenance questionnaire each day during the first four POWs until all normal activities are recovered. This questionnaire indicates their ability to perform daily living activities [19]. The Katz ADL evaluates the patient’s independent performance in six functions: bathing, dressing, using the toilet, transferring, continence, and feeding. These functions are evaluated with yes/no questions. A score of 6 indicates independence in all six functions, demonstrating normal physical activity. Since all donors are able to perform these basic activities before the operation, the Katz ADL questionnaires are not administered prior to surgery. The questionnaires will be gathered at each follow-up visit, and the number of days it takes to return to normal physical activity will be determined based on the answers. The primary endpoint has been defined as the number of days from surgery until return to normal physical activity.

#### Secondary endpoints

Intraoperative outcomes, including estimated blood loss, warm ischemia time, and operating time, will be reported. In addition to the Katz ADL questionnaire, a physical activity score will be determined using the International Physical Activity Questionnaire-Short Form (IPAQ-SF). The IPAQ-SF score will be calculated before the operation and at POWs 2, 4, and 8. Postoperative pain will be assessed using the visual analog scale (VAS 0–10, 0 = no pain and 10 = unbearable distress) and by measuring in-hospital rescue analgesics until discharge. The peak expiratory flow rate (PEFR) will also be evaluated preoperatively and until discharge as an objective surrogate measure of pain. Length of hospital stay, time to return to work, postoperative complications, and all-cause mortality will also be reported in living donors. The appearance of incision scars will be evaluated with a patient satisfaction score (Likert scale 1–5, with 5 indicating strongly satisfied and 1 indicating strongly unsatisfied) and a cosmetic score (defined by the Stony Brook Scar Evaluation Scale [20]) during the first eight POWs. Possible incisional hernia at the site of the surgical incision will be examined by palpation and ultrasonography during each visit. The quality of the procured graft will also be evaluated in recipients after both procedures. Delayed graft function, primary non-function, serum creatinine levels, and glomerular filtration rates will be assessed in recipients until POW 4. Secondary outcome measures are defined in Table 1.

**Table 1 Tab1:** Secondary endpoints of the HAPERPACT trial

Secondary endpoints	Definitions
Warm ischemia time	From the time of clamping the first renal artery in situ to flushing the kidney with chilled solution on the back table (minutes)
Intraoperative complications	Any complication occurring during the operation
Estimated blood loss	The entire blood loss from skin incision to skin closure (milliliters)
Operating time	From the time of skin incision to closure of the skin incision (minutes)
Postoperative pain	Severity of pain measured by the 11-point visual analog scale (0 = no pain and 10 = unbearable distress)
Rescue analgesic	Total amount of analgesics required during the first three postoperative days
Peak expiratory flow rate (PEFR)	Maximum speed of expiration, measured with a peak flow meter
Postoperative complications	Postoperative surgical complications (i.e., burst abdomen and hernia, wound infection, seroma, and hematoma, intra-abdominal bleeding/hematoma, intra-abdominal abscess or collection, lymphocele, and postoperative ileus) and medical complications (pneumonia, pleural effusion, urinary tract infection). Each complication will be graded according to the Clavien-Dindo classification [29]
Length of hospital stay	From the day of the operation until the day of discharge (days)
Time to return to work	The number of days from discharge to return to work
IPAQ-SF score*	The physical activity of patients will be evaluated preoperatively, and on postoperative weeks 1, 2, 4, and 8 using the IPAQ-SF [18]
Patient satisfaction score	Patient satisfaction score measured by the 5-point Likert scale (5 = strongly satisfied and 1 = strongly unsatisfied)
Cosmetic score	Cosmetic score as defined by the Stony Brook Scar Evaluation Scale [20]
Incisional hernia	Fascia or muscle defect (bulging hernial sac and palpable fascia gap) at the site of the surgical incision examined by palpation and ultrasonography
Mortality	Death due to any cause at any time during the follow-up period
Primary non-function (PNF)	The graft never functions
Delayed graft function (DGF)	The need for one or more hemodialysis treatments following transplantation prior to the onset of graft function. The duration of DGF will be calculated from the date of transplantation to the date of the last dialysis treatment
Recipient serum creatinine level	Serum creatinine level (mg/dL)
Glomerular filtration rate (GFR)	GFR (mL/min/1.73 m^2^) calculated as 175 × (S_cr_)^–1.154^ × (Age)^–0.203^ × (0.742 if female)

**IPAQ-SF* International Physical Activity Questionnaire-Short Form

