### Standardized therapy and trial interventions

The site of hand-port placement will be randomized. All other intraoperative and perioperative treatments are standardized procedures. Prophylactic antibiotic therapy and use of intravenous or oral analgesic agents to relieve postoperative pain will be administered according to our kidney transplantation manual [21].

According to the randomization arm, hand-port placement and hand insertion will be via a midline periumbilical or Pfannenstiel incision. HALDN with a periumbilical incision will be performed by positioning the donor in a left/right lateral decubitus position. A 5-mm laparoscope port will be placed at the midclavicular line in the left/right upper quadrant (two finger breadths below the costal margin), and one working instrument (12 mm) will be placed at the level of the umbilicus to the left/right of the midline. HALDN with a Pfannenstiel incision will be performed by placing the donor in the French position. A four-port transperitoneal approach will be used: a 10-mm umbilical trocar for the laparoscope, one 5-mm port in the midline, one 12-mm port at the level of the umbilicus to the left/right of the midline, and an additional 5-mm port will be inserted at the left/right border of the Pfannenstiel incision. As soon as the blood vessels are divided and the nephrectomy is completed, the graft will be extracted using the hand port. At the end of the operation, an abdominal drain will be placed and the wound will be closed.

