### Assessment of safety and termination criteria

To assess the safety of the periumbilical and Pfannenstiel approaches, serious adverse events (SAEs) will be observed and evaluated. Only intervention-related events that occur during surgery and follow-up will be documented. At each visit, the physician will ask the donor if he/she has suffered from any SAEs since the last visit. The attending physician must tell the principal investigator about any reported SAEs within 24 h. The report will be complete and include details of the SAE and whether the SAE was caused by the trial treatment. All intervention-related SAEs will be documented and analyzed.

Donors will be excluded from the study if they withdraw their consent to participate in the trial. A donor may withdraw consent at any time without explanation and without affecting further medical care. The principal investigator may terminate the trial at any time in consultation with the key research associates and the biostatistician. Possible reasons for termination include high morbidity or mortality rates and any indication of potential health hazards caused by either the study treatment or external factors.

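### Table 1 words postoperative complications as an exhaustive list, so an unlisted complication has no stated place in the graded comparison

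*Protocol article*

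**What the plan says.** The Secondary endpoints section says that postoperative complications will be reported in donors and then hands the definitions to the table: "Secondary outcome measures are defined in Table 1".

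The postoperative row of Table 1 has two parts. The surgical part reads "Postoperative surgical complications (i.e., burst abdomen and hernia, wound infection, seroma, and hematoma, intra-abdominal bleeding/hematoma, intra-abdominal abscess or collection, lymphocele, and postoperative ileus". The row then continues "and medical complications (pneumonia, pleural effusion, urinary tract infection). Each complication will be graded according to the Clavien-Dindo classification". Neither part contains *for example*, *including* or *other*.

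Two other safety rows in the table are worded openly. Intraoperative complications are "Any complication occurring during the operation", and mortality is "Death due to any cause at any time during the follow-up period".

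Outside the table, Assessment of safety and termination criteria says that donors are asked about SAEs at each visit and that "All intervention-related SAEs will be documented and analyzed". The same section restricts documentation to events related to the intervention. The Statistical analysis section treats all secondary outcomes with summary measures and descriptive p values.

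**The concern.** The article does more than leave complication coding to a later document. It states a definition and makes Table 1 its home. In that definition *i.e.* means *that is*, so the surgical events read as the complete set, and the three medical events stand without any qualifier. Clavien-Dindo grading is then applied to each member of that set. It adds a severity grade but does not reopen the list.

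The Background treats a low complication rate in a healthy donor as being as important as graft quality, and the abstract says the findings will help decide which procedure is best for donors. The complications row carries much of that comparison. If it is applied as worded, complications that nobody thought to list do not enter it.

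**Working it through.** **Is the list closed?** Counting the entries in the row:

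- Surgical: 8 if burst abdomen and hernia count as one entry, 9 if they are separate.
- Medical: 3.
- Total: 8 + 3 = 11, or 9 + 3 = 12.

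Thromboembolism is not among them, and no wording admits further events.

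**Where would a complication in a donor be recorded?**

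| Event | Place the article gives it |
|---|---|
| Listed postoperative event | Postoperative complications, graded by Clavien-Dindo |
| Injury occurring during surgery, listed or not | Intraoperative complications (open wording) |
| Death from any cause | Mortality (open wording) |
| Unlisted postoperative event, serious and intervention-related | SAE documentation and analysis; not stated to enter the graded comparison |
| Unlisted postoperative event, serious but judged unrelated | None stated |
| Unlisted postoperative event, not serious | None stated |

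The gap is therefore the last two rows, plus the fact that the SAE row runs in parallel to the graded endpoint and does not feed it.

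**How large could it be?** The article gives no complication rate, so there is no plan figure to reproduce for this endpoint. The only input it supplies is the number enrolled per arm. From the Sample size section, 22 per group with 15% drop-out gives 22 / (1 − 0.15) = 25.9, rounded up to 26, which agrees with the stated number. With 26 donors in the denominator, one donor left out moves an arm's complication rate by 1/26 = 0.038, or 3.8 percentage points. The number of donors affected cannot be derived from the documents.

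**Does it reach the primary analysis?** No. The sample size rests on a 10-day difference, a standard deviation of 13 days, one-sided 5% and 80% power for days to normal physical activity. None of these depends on how complications are defined.

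**The case against.** The strongest reply is that this is a drafting slip in a condensed article. The text of the Secondary endpoints section announces postoperative complications without restriction, and the open wording of the neighbouring rows suggests that the authors wanted an open definition here too. The case report form may already carry a free-text line for other complications, and the analysis plan, which is due by the end of recruitment, may settle the coding. Neither is shown. The endpoint is also one of many that are analysed descriptively.

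Much of this stands, and it limits the point to a minor one. It does not remove it. The article states a definition rather than deferring one, and if the case report form is broader, the published definition disagrees with it and still needs correcting.

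Three stronger readings are tempting, and the documents do not support them:

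- **Unlisted events are scored as no complication.** The article contains no such rule. It does not say how they are classified.
- **Bowel, nerve or positioning injuries are lost, and could differ by arm.** The arms do differ in position: for one of them "HALDN with a Pfannenstiel incision will be performed by placing the donor in the French position", while the other uses lateral decubitus. But an injury that occurs during the operation falls under the open intraoperative row, which turns on when the event happened and not on when it was recognised.
- **Severe events are hidden.** Serious intervention-related events are documented and analysed as SAEs without a list of named events, and any death falls under all-cause mortality.

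**Conclusion.** The point holds as a minor defect of definition. On its wording the postoperative row is exhaustive, unlike the intraoperative and mortality rows, and unlisted postoperative complications are outside the graded comparison. Those that are non-serious or judged unrelated have no stated place in any endpoint; those that are serious and related are captured only through SAE reporting.

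The size is bounded only per donor: 3.8 percentage points of an arm's rate for each donor left out, assuming 26 donors in the denominator. A reader might multiply an assumed complication rate by an assumed share of unlisted events to obtain an under-count. The documents give neither input, so such a figure would show only what was assumed. They also give no basis for saying that an arm difference would be concealed.

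The conclusion rests on reading Table 1 literally, as the Secondary endpoints section invites. It has no bearing on the primary endpoint, its test or the sample size.

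**What to change.** In the postoperative row of Table 1, define the endpoint as any postoperative complication during follow-up, graded by Clavien-Dindo. Replace *i.e.* with *including*, keep the named events as pre-specified categories, and add an other category for surgical events and another for medical events. An unlisted event that is also an SAE then enters the graded comparison as well as the SAE report.

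The cost is one sentence in the table and, if the case report form does not already have it, an other-specify line for each category. The downside is a slightly higher reported complication rate.

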### Randomization and blinding

Donors will be randomized to the different groups using the block randomization method. Each block contains two groups of periumbilical and Pfannenstiel incisions. The block size is hidden from the trial executers and clinicians. Possible balanced combinations of these groups within the block are numbered consecutively. Then, blocks are randomly chosen using simple randomization software (Microsoft Excel®), and a series of randomly assigned periumbilical and Pfannenstiel incisions are generated based on the random sequence of blocks. Allocation will be concealed using sequentially numbered, sealed opaque envelopes prepared by a member of our Clinical Trial Center. Donors will be randomly allocated to either the control arm (periumbilical incision, Group A), or the intervention arm (Pfannenstiel incision, Group B) a day before surgery. The trial executors receive randomly generated treatment allocations within sealed opaque envelopes. Afterwards, medical staff will personally inform the expert surgeon as to which treatment group the patient has been randomized. To avoid any potential prediction of group allocation, information on the block length will be kept away from the study site.

After the operation, the periumbilical and hypogastric regions will be covered with a double wound dressing until discharge. During this period, the severity of pain, rescue analgesic, and PEFR will be evaluated by anesthesiologists blinded to the incision type. Participants will also be blinded to the incision type. If blinding could affect the patient’s treatment, for example in the case of a medical emergency or serious medical condition, then the participant/assessor will be unblinded. After POD 4, a nephrologist who is unaware of the study will evaluate and document the primary and secondary endpoints of the trial. At the end of the trial, the data management center will receive all sealed envelopes and will check the accuracy of randomization numbers.

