### Statistical methods

#### Sample size

The null hypothesis is that Pfannenstiel incision is not superior to periumbilical incision in terms of the average number of days it takes the donor to return to normal physical activity in the 4 weeks after surgery. We chose 10 days difference in return to normal physical activity as the minimal clinically important difference, because a difference of less than 10 days is not valuable enough to decide the standard surgical method. Therefore, we used a difference of 10 days for sample size calculation. The standard deviation is expected to be 13 days, according to the results of El-Galley et al. [15], who compared days to return to work between periumbilical and Pfannenstiel incision groups. However, we chose “days to return to normal physical activity” as the primary endpoint rather than “days to return to work” because the nature of patients’ work and their capabilities are different, and some of our living donors may be unemployed or housekeepers. A one-sided significance level of α = 0.05, a power of 80%, and a sample size of 44 patients (22 per group) are required to apply a two-sample *t* test (calculations performed with AddPlan 6.0). To account for a 15% drop-out rate, 26 patients will be enrolled in each study arm (52 patients in total).

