#### Statistical analysis

The primary endpoint is the number of days from surgery to return to normal physical activity. This will be assessed using the Katz ADL questionnaire. The primary analysis will test the following hypotheses:

H_0_ μ_Pfannenstiel_ ≥ μ_Periumbilical_

H_1_ μ_Pfannenstiel_ < μ_Periumbilical_,

where μ_Pfannenstiel_ and μ_Periumbilical_ are the mean number of days in the respective intervention groups. The primary endpoint will be compared between the intervention groups using a Student’s *t* test and a one-sided significance level of 5%. Additionally, a Mann-Whitney *U* test will be performed for sensitivity analysis. According to the intention-to-treat approach, all patients will be analyzed in the group to which they were randomized.

All secondary outcomes will be analyzed using appropriate summary measures depending on the distribution of the data and descriptive *p* values. Categorical data will be presented as absolute and relative frequencies. Continuous data will be presented as mean values with standard deviations and by median values with interquartile ranges, minimum values, and maximum values. Statistical analysis will be performed using SPSS version 24.0 (SPSS, Inc., Chicago, IL, USA). A statistical analysis plan will be developed by the principal investigator by the end of recruitment.

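### Time to return to work is counted from discharge, so any between-arm difference in hospital stay would shift the comparison against the arm discharged earlier

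*Protocol article*

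**What the plan says.** The protocol article fixes the start of the clock in Table 1 (Secondary endpoints), where time to return to work is "The number of days from discharge to return to work". The row directly above it defines length of hospital stay: "From the day of the operation until the day of discharge (days". The two intervals meet at discharge, and each is a separate secondary endpoint.

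The other recovery time in the trial starts elsewhere. Under Primary endpoint it is the "number of days from surgery until return to normal physical activity", and Statistical analysis repeats that origin. Under Randomization and blinding, donors are allocated "a day before surgery", so discharge always comes after allocation.

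On analysis, the article says: "All secondary outcomes will be analyzed using appropriate summary measures depending on the distribution of the data and descriptive" *p* values. No section counts return to work from surgery or adjusts it for length of stay. Statistical analysis adds that an analysis plan will be developed by the end of recruitment.

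**The concern.** A randomised comparison of a duration is fair when the clock starts at randomisation or at a point the treatment cannot move. Surgery, one day after allocation, meets that test for practical purposes. Discharge does not: it depends on the early postoperative course, which the incision may affect, and the trial itself treats it as an outcome.

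Counting from discharge removes the hospital days from the measure. A donor sent home sooner starts the clock sooner and, for the same date of return to work, is recorded as taking longer. If one incision shortens both the stay and the absence from work, the benefit in stay is deducted from the benefit in return to work. The Discussion lists return to work among the factors bearing on donor satisfaction and refers to economic impact. For those purposes the absence that counts begins at the operation.

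**Working it through.** **Inputs.** Time origin of return to work: discharge (Table 1). Length of stay: operation day to discharge day (Table 1). Time origin of the primary endpoint: surgery (Primary endpoint; Statistical analysis). Sample size inputs: difference 10 days, SD 13 days, one-sided 5%, power 80%, 15% dropout (Sample size). Difference in stay between arms: not given in the documents, so assumed here to lie between 0 and 3 days.

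**1. The plan's own figure.** The point disputes no stated number, but the planning figure was checked to see whether it depends on this definition. A one-sided two-sample *t* test with difference 10 and SD 13 has power 0.7897 at 21 per arm and 0.8065 at 22 per arm, so 22 is reproduced. With 15% dropout, 22 / 0.85 = 25.9, rounded up to 26 per arm and 52 in total, as stated. All inputs belong to the primary endpoint, so the clock in Table 1 does not enter.

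**2. The identity.** For each donor who returns to work:

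discharge-to-work = surgery-to-work − length of stay.

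Taking means and subtracting one arm from the other, over the same donors:

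difference(discharge-to-work) = difference(surgery-to-work) − difference(length of stay).

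The last term is the shift. It is exact for means; for medians the equality need not hold exactly.

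**3. No true difference.** Suppose both arms average 30 days from surgery to work (an assumed value that cancels out). With stays of 5 and 3 days, the discharge-based means are 30 − 5 = 25 and 30 − 3 = 27. The arm discharged 2 days earlier looks 2 days slower, although the difference from surgery is 0. Over the assumed range of 0, 1, 2 or 3 days in stay, the spurious delay is 0, 1, 2 or 3 days.

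**4. A true gain.** Let one arm return to work g days sooner after surgery and have a stay d days shorter. Its gain as measured from discharge is g − d (negative means that it appears slower):

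| True gain g (days) | d = 1 | d = 2 | d = 3 |
|---|---|---|---|
| 1 | 0 | −1 | −2 |
| 2 | 1 | 0 | −1 |
| 3 | 2 | 1 | 0 |
| 5 | 4 | 3 | 2 |
| 10 | 9 | 8 | 7 |

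The measured gain is understated when g exceeds d, cancelled when they are equal, and reversed when g is smaller than d.

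**5. Scale against sampling error.** If the 13-day SD also applied to this endpoint (an assumption), the standard error of the difference would be 13 × √(2/22) = 3.9 days at 22 per arm and 13 × √(2/26) = 3.6 days at 26 per arm. A 2-day shift is then about half a standard error (2/3.9 = 0.51; 2/3.6 = 0.56).

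**6. After the change.** Counted from surgery, the length-of-stay term drops out. The difference in step 3 is 0 for every value of d, and step 4 returns g.

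**The case against.** The strongest reply is that little depends on this row. It is one of 19 in Table 1, it receives descriptive *p* values only, and under the SD assumption above a 2-day shift is well within sampling error. Nothing is lost either: the two intervals are contiguous and both are recorded, so adding them gives surgery-to-work time for each donor. Splitting recovery into a hospital part and a home part is also an intelligible description.

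All of this limits the weight of the point, but none of it removes it. The shift is systematic and does not average out, and the definition as written is the one that would be reported. The split works as a description but not as a between-arm comparison of return to work. Nor is this a detail left open for the analysis plan, because the article states the time origin outright.

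Three stronger readings are tempting, and the documents do not support them.

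- A reader might infer that the definition does make one arm look slower. That holds only if mean stay differs by arm, and the documents give no expected stay for either.
- A reader might infer that the planning SD or the case for the Pfannenstiel incision is undermined. The SD comes from an external study and is applied to the primary endpoint, so the origin in Table 1 has no bearing on it. The Background also cites wound complications and cosmetic outcomes in favour of that incision.
- A reader might infer a further fault in the lack of a rule for donors without a job or not yet back at work by the last visit in postoperative week 8. Sample size acknowledges that "some of our living donors may be unemployed or housekeepers", and a condensed article may leave such handling to the analysis plan.

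**Conclusion.** The point holds in conditional form. Table 1 starts the return-to-work clock at a post-randomisation date that is itself the end of another outcome, and no other section corrects this. If mean stay differs between arms, the difference in mean return-to-work time is displaced by exactly that amount, against the arm discharged earlier. If stay does not differ, there is no displacement.

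The 0 to 3 day size rests on an assumed range of differences in stay. Within that range, a large benefit is understated and a small one can be cancelled or reversed. The consequence is confined to the reading of one secondary endpoint. The change is still worth making, because it removes an avoidable bias at almost no cost.

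**What to change.** Define time to return to work as the number of days from the day of surgery to the first day back at work, in donors who were working before surgery. Write this into the analysis plan that is still to be developed, and correct Table 1 at the next protocol amendment. The discharge-based interval may be kept as a descriptive supplement, labelled as such.

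No new dates are needed: length of stay already uses the operation and discharge dates, and the present definition already requires the date of return to work. The restriction needs pre-operative work status, which has to be known for the present definition to make sense as well.

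The small downside is procedural. Under Modification of the protocol, amendments go to the Ethics Committee and recruitment pauses until they are accepted, and Trial status says that recruitment is under way. That is the reason to use the analysis plan now and to carry the change to Table 1 with the next amendment, without opening one for this alone.
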